**RISK ANALYSIS, POSSIBLE PROBLEMS AND SOLUTIONS**

The main risk related to Aim1 is the failure of the statistical validation process of the new method compared to gold standard. For this reason, it has been decided to proceed to an *ad interim* analysis (at month 12). If data is not satisfactory, physicists will revise the engineering of the software and/or the precision of the physical model before continuing the experiment.

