**EXPERIMENTAL DESIGN AIM 1**

Aim 1 will be divided into 2 phases.

Phase 1: improvement and refinement of US-JVP software usability.

In a preliminary experiment (10) the variation of the cross-sectional area of the IJV during the cardiac cycle by means of real time B-mode images sequence was studied, and a resultant waveform trough time was outlined. It was also verified if an automatic procedure could reliably substitute a time inefficient operator tracing. Thanks to an algorithm and the development of a related original software, it was tested that the assessment of this waveform can be performed in post-processing analysis. This first phase of the project will be devoted:

a) To improve the usability of the algorithm and related software.

b) To study the relationship between variations of IJV cross sectional area and variations of IJV inside pressure in order to develop a physical model providing an estimate of the CVP.

c) To study the different waveforms derived from the US-JVP outlining a pool of normal or potential diagnostic abnormal patterns.

This will lead to further refinement of the algorithm and the related software in view of the Phase 2 of the project and the final validation of the US-JVP technique. This first phase will be carried out by close collaboration among physicists and clinicians.

Setting

OU of Translational Surgery and OU of University Anesthesiology and Intensive care, University Hospital of Ferrara and Eco-Fluid dynamics lab of the Department of Physics, University of Ferrara.

Subjects

At least n=80 consecutive healthy adult subjects of different sex and age will be studied by means of US-JVP technique. This number of subjects will likely allow us to detect and to evaluate the different morphological subtypes of IJVs.

Inclusion criteria: adult subjects (> 18 years).

Exclusion criteria: current acute disease, chronic cardiac or lung diseases, neurodegenerative diseases, pregnancy.

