The validation processes will include assessment of the diagnostic power of the US-JVP estimated CVP values and US-JVP waveforms, including evaluation of sensibility, specificity, predictive positive and negative values, accuracy and precision, compared to the gold standard of direct invasive measurement of CVP.

Setting

OU of Translational Surgery and OU of University Anesthesiology and Intensive care, University Hospital of Ferrara and Eco-Fluid dynamics lab of the Department of Physics, University of Ferrara.

Subjects

n= 150 consecutive hospitalized spontaneously breathing patients requiring a scheduled, or with deferred emergency, measurement of CVP by direct cannulation.

Inclusion criteria: hospitalized adult > 18 years in spontaneous breathing requiring a direct measurement of the CVP, scheduled or in a deferred emergency.

Exclusion criteria: no clinical exclusion criteria. Pregnancy,

Methods

All patients will undergo a US scanning of the neck at bedside as described above, performed independently and sequentially by two skilled operators to verify the inter-observer reliability. To verify the test-retest reliability, operators will repeat the procedure twice and two 30”clips will be recorded. Operators will be blinded to the respective evaluations, to the clinical condition of the patient and to the subsequent measures of invasive CVP. Immediately afterwards CVP assessment by direct cannulation of the venous system will be performed by competent staff operators according to the standard.

For all the phases of the study, the measurement of CVP will not be carried out for experimental purposes but will be part of the scheduled plan for each subject during the hospitalization. Only the numerical data obtained will be considered for the purpose of this study. Therefore, no variation is expected with respect to the normal diagnostic-therapeutic pathway already defined for each study subject.

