**STATISTICAL ANALYSIS**

Aim1-Phase 1. Descriptive data will be expressed as the mean ± standard deviation or median and range according to the nature of the variables.

Aim1-Phase 2. The new US-JVP method will be compared to the gold standard of invasive CVP measurement in patients from an intensive care unit, with operators blinded to the patient’s condition and values of the direct measure of CVP. The number of patients required to estimate sensitivity and specificity, in a target population with a prevalence of 50%, assuming a clinically acceptable width of the 95% confidence interval of 10%, and a sensitivity and a specificity at least both of sizes 0.80, is 123. In order to correct for missing values, we will collect 20% patients more for a total sample size of 150 (11). Correlation between the two methods (US-CVP) will be analyzed using Pearson’s coefficient. The Bland-Altman method will be used to analyze the agreement between the measurements. The validation processes will assess the diagnostic power of the US-JVP evaluating sensitivity, specificity, predictive positive and negative values, accuracy and precision. Receiver operating characteristic (ROC) curves will be used to assess the sensitivity and specificity corresponding to different cutoffs for the new US-JVP method. Inter observers and test-retest reliability will be also calculated.

Aim 2 – Phase 3. The sample size needed to assess reliability between operators is based on Walter et al. (12). Assuming a minimally acceptable level of reliability of 0.60, given an alternative hypothesis of a level of reliability of 0.80, an alpha level of 0.05, a power of 0.80, a total of 40 patients are necessary to be evaluated independently by each clinician. Intraclass correlation coefficient (ICC) will be determined.

Aim 2 – Phase 4. Intraclass correlation coefficient (ICC) will be determined after the training. The Bland-Altman method will be also used to analyze the agreement between clinicians.

The statistical approach and analysis will be followed and carried out by statisticians of the Department of Public Health, Experimental and Forensic Medicine, Unit of Biostatistics and Clinical Epidemiology, University of Pavia

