**Timeline/ Milestones**

-0-6 months period: Definitive implementation of the US-JVP technique (Aim 1-Phase1).

-6-18 months period: Full validation of the US-JVP technique (Aim 1-Phase 2).

-18-21 months period: Data analysis Aim 1.

-21-33 months period: Evaluation of the transferability of the US-JVP technique in a multidisciplinary clinical setting (Aim 2-Phase 3 and Phase 4).

-33-36 months period: Data analysis Aim 2 and dissemination of the overall scientific results.

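### The month-12 interim allows the software or model to be revised halfway through validation, with no rule on which patients then validate the revised version

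*Protocol*

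**What the plan says.** The timeline in the Protocol separates development from validation. Phase 1 is given as "0-6 months period: Definitive implementation of the US-JVP technique (Aim 1-Phase1") and Phase 2 as "6-18 months period: Full validation of the US-JVP technique (Aim 1-Phase 2"). The Aim 1 design section agrees. It says of the Phase 1 work: "This will lead to further refinement of the algorithm and the related software in view of the Phase 2 of the project". The 18-month milestone likewise places refinement of the software and the physical model in the first six months.

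The risk section opens with this: "The main risk related to Aim1 is the failure of the statistical validation process of the new method compared to gold standard". It answers that risk with an interim "analysis (at month 12") and gives the action to follow: "If data is not satisfactory, physicists will revise the engineering of the software and/or the precision of the physical model before continuing the experiment". It sets no criterion for a satisfactory result.

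The Phase 2 design describes a single cohort, "n= 150 consecutive hospitalized spontaneously breathing patients". The statistical section sizes it at 123 and then adds an allowance: "we will collect 20% patients more for a total sample size of 150". That section lists one set of Phase 2 analyses (correlation, Bland-Altman, sensitivity, specificity, predictive values, ROC). It does not mention the interim, software versions or a revision.

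**The concern.** A validation sample does its job only if the test was fixed before the sample was examined and stays fixed while it is collected. Here the comparison with invasive CVP can feed back into the test under validation, halfway through. This conflicts with the Protocol's own division between Phase 1 and Phase 2.

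After a revision there are two ways to use all 150 patients, and neither gives a clean estimate for the final version:

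- **Earlier patients keep their old results.** The pooled sensitivity, specificity, ROC curve and limits of agreement then mix two index tests and describe neither.
- **The stored 30-second clips are re-read with the revised version.** There is then one test, but the patients enrolled before the interim helped to shape it, so their apparent accuracy tends to be optimistic.

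At stake is the main result of Aim 1, the accuracy of US-JVP against the gold standard. Once early patients have informed a revision, they cannot be made independent of it again, so the rule has to be in place before month 12.

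**Working it through.** **Inputs from the Protocol.** Phase 2 runs from month 6 to month 18, and the interim is at month 12. Prevalence is 0.50, sensitivity and specificity are 0.80 each, and the 95% confidence interval figure is 10%. The requirement is 123 patients, raised to 150.

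**Timing.** (12 − 6) / (18 − 6) = 0.5, so the interim falls exactly at the calendar midpoint of Phase 2.

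**The plan's own figure.** The precision formula for one proportion, divided by prevalence, gives

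n = 1.96² × 0.80 × 0.20 / 0.10² / 0.50 = 122.9, so 123.

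This reproduces the plan if the 10% is read as a half-width; a full width of 10% would need 492. The allowance is 123 × 1.2 = 147.6, rounded to 150. The implied evaluable fraction is 123/150 = 0.82. The calculation assumes one fixed test in one independent sample.

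**Precision from post-revision patients only.** The half-width is 1.96 × √(0.16 / (0.5 × evaluable patients)). The share enrolled by month 12 is not in the documents. Even accrual is assumed, with a range of one third to two thirds.

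| Enrolled by month 12 | Remaining | Evaluable at 0.82 | Half-width |
|---|---|---|---|
| one third | 100 | 82 | 1.96 × √(0.16/41) = 12.2 points |
| one half | 75 | 61.5 | 1.96 × √(0.16/30.75) = 14.1 points |
| two thirds | 50 | 41 | 1.96 × √(0.16/20.5) = 17.3 points |

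If all 75 later patients were evaluable, the half-width would be 1.96 × √(0.16/37.5) = 12.8 points. The like-for-like comparison with the planned 10, which rests on 123 evaluable of 150, is 14.1.

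**Mixing two versions (illustration, assumed values).** Sensitivity of 0.70 before and 0.80 after the revision, split 50:50, pools to 0.5 × 0.70 + 0.5 × 0.80 = 0.75. That is true of neither version and lies below the revised one.

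**Re-reading the clips (illustration, assumed tuning).** A simulation took true sensitivity and specificity of 0.80 and 123 evaluable patients, and made the choices on the first half. Apparent accuracy in that half was 0.83 when only a cutoff was chosen, and 0.88 when the best of four equally good models was also picked. The untouched half gave 0.79 in both cases, and the pooled figure was 0.81 to 0.83. This shows the direction of the error. Its size depends on the assumed tuning.

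**Keeping 10 points.** This needs 123 evaluable, so 150 enrolled, after the lock: 75 + 150 = 225 in total under even accrual, or 200 to 250 over the same range.

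**The case against.** The strongest reply is that the Protocol never says that patients before and after a revision will be pooled. Continuing the experiment is compatible with validating the revised version in later patients only, and analysis sets after a contingency could be defined in an SAP, which is not at hand. The first part stands: pooling is an inference from the single cohort of 150 and the single set of analyses. The second part does not remove the problem. The interim, its consequence, the cohort and its size are all fixed in the Protocol. Whether early patients still count as validation data determines how many independent patients the stated sample contains.

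A reader might also infer that the accuracy figures will necessarily look too good, by some predictable number of points. The documents do not support that. Optimism follows only if clips are re-read with the revised version and pooled. If earlier patients keep their old results, a poor first half pulls the pooled figure down and may understate the revised version. Nothing in the Protocol fixes the size of either error.

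Finally, the problem is conditional. If the interim is judged satisfactory and nothing is changed, the planned analysis is unaffected by it. That is correct, but the Protocol itself names failure of validation as the main risk of Aim 1, so a revision is its planned response.

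**Conclusion.** The point holds. The Protocol allows the software or model to be re-engineered in the middle of its validation phase, in response to the validation comparison, and sets no version lock, split or restart. As written, an analysis of all 150 after a revision would be a mixture of two tests or a partly tuned result, with bias of undetermined size and, across the two routes, of either direction.

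The measurable consequence is precision. An independent estimate for the revised version has a half-width of about 14 points instead of 10. This assumes even accrual, 82% evaluable, prevalence of 0.50 and true sensitivity and specificity of 0.80. The range is about 12 to 17 points if one third to two thirds are enrolled by month 12. The conclusion does not depend on these assumptions; only the figure does. The point should be settled before the interim takes place.

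**What to change.** Add the following to the risk section and to the Phase 2 part of the statistical section:

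- The criterion by which the interim result counts as not satisfactory, stated in advance.
- If the software or physical model is changed at the interim, patients enrolled before the change become development data.
- Sensitivity, specificity, ROC and Bland-Altman results for the revised version use only patients enrolled after that version is locked.
- Results for the version locked at the end of Phase 1 are reported separately.
- In that case the expected 95% half-width is about ±14 points (61.5 evaluable of 75, even accrual), or ±12.8 if all 75 are evaluable, instead of ±10. The text should also say that the 10% is a half-width.

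The cost is protocol wording and a log of software versions. The drawback is a wider stated interval if a revision happens. No extra patients are needed if that is accepted; keeping ±10 for the revised version would mean about 225 patients in total under even accrual.

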**SIGNIFICANCE AND INNOVATION**

It is known that the assessment of the JVP for its diagnostic and prognostic power is desirable, despite the fact that it is currently neglected (1-9). The main reason is the uncommon skill required for JVP clinical assessment (4,5). Alternatively, a non-invasive, rapid and at low cost instrumental technique able to comprehensively assess the JVP and CVP at bedside does not exist so far. Completely noninvasive methods have not been reported to have the accuracy and precision necessary for routine use and interchangeability with traditional invasively measured CVP (6). In addition, the technique here proposed, differently from other US methods previously developed to assess the JVP (6-9), might not only be able to provide an estimate value of CVP, but also to outline characteristic wave patterns pathognomic of cardiac diseases. This technique might be useful in a variety of multidisciplinary emergency and elective clinical situations.

**DESCRIPTION OF THE COMPLEMENTARITY AND SYNERGY RESEARCH TEAM**

The project includes a multidisciplinary team of clinicians, technicians, physicists and statisticians with a strong background in the specific topics covered, as well as a history of previous collaborations. Phase 1 will involve investigators expert in hemodynamics and US of the vascular system and physicists to develop a new non-invasive technique to assess the JVP.

Vascular medical expertise and applied physic skill are needed to fully implement the algorithm and the software supporting the new method. The invasive CVP assessments will be performed in an intensive care unit under the supervision of an accountable investigator. Aim 2, testing the transferability of the method, will be carried out in synergy among clinicians of emergency and specialized units and the experts in hemodynamics and US. Skilled US technicians will attend all the experimental phases for the correct images acquisition, as well the statisticians who will be responsible for a load-bearing part of the project.

**Timeline/ Milestones**

-0-6 months period: Definitive implementation of the US-JVP technique (Aim 1-Phase1).

-6-18 months period: Full validation of the US-JVP technique (Aim 1-Phase 2).

-18-21 months period: Data analysis Aim 1.

-21-33 months period: Evaluation of the transferability of the US-JVP technique in a multidisciplinary clinical setting (Aim 2-Phase 3 and Phase 4).

-33-36 months period: Data analysis Aim 2 and dissemination of the overall scientific results.

**Milestones 18 month**

After a first phase (0-6 months) devoted to the full implementation of the US-JVP, in particular for the refinement of the software allowing the automatic evaluation of the JVP and of the physical model for the estimate of CVP, at 18 months we expect the conclusion of the experimental part of Aim 1, namely the validation of the new technique in a clinical setting.

**Milestones 36 month**

In the 18-21 months period the data analysis related to Aim 1 will be performed.

In the 18-33 months period we will carry on with Aim 2 of the project, specifically the verification of the operative transferability of the new method in clinical/emergency settings. The last step period (33-36 months) will be devoted to the final data analysis and dissemination of the overall scientific results.

**EQUIPMENT AND RESOURCES AVAILABLE**

Measurements of US-JVP will be performed by operators specifically trained in PhD programs devoted to the detection of non-conventional parameters of the brain circulation assessed by innovative US techniques. A portable Echo-Color Doppler instrument is available in the O.U. of the PI, while another analogue instrument will be acquired in leasing for the segment of the project at bedside in the other O.Us. Invasive measurements of the CVP will be performed as part of the usual clinical practice by skilled operators under the supervision of an accountable senior investigator. The Eco-Fluid dynamics lab of the Department of Physics-University of Ferrara (which is involved in the project as a scientific supporting part) is equipped with innovative technologies purposely created to study the blood flow in physiological and pathological conditions (e.g. hydraulic circuit that simulates the blood circulation in the neck) staffed by a team of researchers skilled in the analysis of the response of Echo-Doppler flow. The statistical analysis will be performed by the Department of Public Health, Experimental and Forensic Medicine, Unit of Biostatistics and Clinical Epidemiology, University of Pavia. In addition, all the investigators involved in the project have got a consolidated history of previous collaboration.

**TRANSLATIONAL RELEVANCE AND IMPACT FOR THE NATIONAL HEALTH SYSTEM**

In case of positive results, the new US-JVP technique could be proposed in clinical practice for rapid, non-invasive, and cost-effective evaluation of JVP and CVP by means of equipment widely available in the Hospitals of our Country, and by multidisciplinary operators appropriately trained. Cardiovascular US-JVP assessment could be useful in a variety of multidisciplinary emergency and elective clinical situations.
**ETHICAL ASPECTS**

To each patient, the investigator will describe the study in detail and read the information sheet allowing him to ask questions whenever a part is difficult to understand. Subsequently, he will be provided with the Consent Form which he is required to read before signing. Patient data will be processed in full compliance with the privacy protection law. They will then be recorded, processed and archived in order to guarantee their security and confidentiality and when included in publications and / or presentations at scientific conferences they will be subjected to statistical processing and then transformed into anonymous data.
